**Table 2 T2:** **The interview questions for the MCI participants at post-intervention (T2) and 1-year follow-up (T3)**.

**Qn**	**Post-intervention (T2)–30 min**	**1-year follow-up (T3)–30 min**
1	Can you please describe your general health for me?	
	I really appreciate you sharing your views.	
2	Can you tell me as much as possible how has the mindfulness training program experience been for you?	
	*[Interviewer's prompts: satisfactory? stimulating? useful?]*	
3	What did you like or enjoy about the program?	
	What did you not like about the program?	
	From your perspective, how can we improve the mindfulness training program experience for future participants?	
4	Can you please tell me how you practice mindfulness?	
	How do you use mindfulness in your day-to-day life?	
5	Can you please tell me what has helped or hindered your mindfulness practice?	
6	Can you please tell me in as much detail as possible how you have been since practicing mindfulness?	
	*[Interviewer's prompts: cognitive function, psychological health, functional abilities and quality of life]*	
7	From your perspective, how did your mindfulness practice influence your health and life?	
	*[Interviewer's prompts: cognitive function, psychological health, functional abilities and quality of life]*	
8	Do you think you would continue to practice mindfulness?	
	How long would you continue?	
9	Do you need any ongoing support and reminders to maintain regular mindfulness practices after the program?	Do you need any ongoing support and reminders to continue regular mindfulness practices from now on?
	If yes, what kind of ongoing support and reminders?	If yes, what kind of ongoing support and reminders?
10	What advice would you give to other people like yourself about undertaking mindfulness training?	What advice would you give to other people like yourself about practicing mindfulness?
11	Can you please describe the role of your familiar support person in the mindfulness training program and outside the program?	Can you please describe the role of your familiar support person for the past year after the mindfulness training program?
12	Any questions or comments you would like to make?	

**Table 3 T3:** **The interview questions for the Familiar Support Persons (FSPs) at post-intervention (T2) and 1-year follow-up (T3)**.

**Qn**	**Post-intervention (T2)–30 min**	**1-year follow-up (T3)–20 min**
1	What has it been like supporting (first name of the MCI participant)?	

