	I really appreciate you sharing your views.	
2	From your personal perspective, how has the mindfulness training program experience been for you?	
	How about your perspective on the program experience as a familiar support person?	
3	Can you please describe how has attending the program influenced you personally?	How has mindfulness influenced you in the past year?
4	How can we improve the mindfulness training program experience for future familiar support persons?	
5	Can you please describe how (first name of the MCI participant) has practiced mindfulness?	Can you please describe how (first name of the MCI participant) has practiced mindfulness in the past year?
	How do you think (first name of the MCI participant) has used mindfulness in his/her day-to-day life?	How do you think (first name of the MCI participant) has used mindfulness in his/her day-to-day life?
6	From your perspective, how has mindfulness influenced (first name of the MCI participant)'s health and life?	From your perspective, how has mindfulness influenced (first name of the MCI participant)'s health and life in the past year?
	How useful do you think mindfulness has been for him/her?	How useful do you think mindfulness has been for him/her overall?
	*[Interviewer's prompts: cognitive function, psychological health, functional abilities & quality of life]*	*[Interviewer's prompts: cognitive function, psychological health, functional abilities and quality of life]*
7	What do you think about your role in supporting (first name of the MCI participant) in mindfulness practice during and outside the program?	What do you think about your role in supporting (first name of the MCI participant) in mindfulness practice in the past year?
8	Any questions or comments you would like to make?	

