## Anticipated results

Repeated measures analysis of variance will be used to test the relative effects of formal and informal mindfulness practices on changes in the following dependent variables, namely cognitive function, psychological health, mindfulness, and ADL functioning from pre- to post-intervention and from post-intervention to 1-year follow-up, with an experiment-wise error rate of 0.05. Normally, each ANOVA should be evaluated with an adjusted (for e.g., Bonferroni correction) decision-wise error rate for possible inflation of Type I error. However, Type I error rate will not be adjusted for these analyses, on the grounds that this is an exploratory study of which any possible effects should be examined by further research. Regression analysis will be used to determine the predictive values of measures of formal and informal mindfulness practices on the changes in the same dependent variables (cognitive function, psychological health, mindfulness, and ADL functioning). Age, gender, and education will be entered into the regression analysis to identify possible moderating effects. The MCI participants' demographics, health and lifestyle information will be examined in relation to the outcome measures in order to interpret the results in context. However, possible trends instead of statistically significant results could be determined from the quantitative analysis. As such, the mixed-methods design of this study enables the qualitative findings to complement the quantitative results in greater depth so that their findings could inform each other and be integrated to better address the research questions. The IBM Statistical Package for the Social Sciences software package will be used for the statistical analysis of the quantitative data.

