Qualitative data analyses by researchers (WW) and [name] (JC) will entail the investigation of the participant observational field notes and the semi-structured interview transcripts. To safeguard privacy, any identifiable information such as the name of the MCI participant, FSP, CDAMS, health service, GP and treating health professional in the audio recording of the interviews will be coded (but re-identifiable by the researchers for qualitative data analyses) in the interview transcripts. The QSR International NVivo software will be used to perform thematic analyses for the identification of important patterns/themes. The iterative (repeating) and inductive (bottom up) process of thematic analysis in the qualitative data analysis phase breaks the data into “smaller chunks” and assigns names or “codes” that summarize the idea within the data chunk (Hansen, 2006; Liamputtong, 2013). The codes are then refined by comparing, sorting and reflecting on the meaning and subsequently developed into “themes”^1^. A coding framework will be developed to provide definitions of the codes and maximize coherence among the codes for coding the qualitative data and generating themes or categories (Creswell, 2014). For inter-coder reliability, codes developed by researchers (WW and JC) will be cross-checked for agreement in coding with the same or similar code in order to maintain consistency in coding (Creswell, 2014). The framework of the presentation of both qualitative and quantitative data is illustrated in Figure 2.

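### The interview guide prompts mostly for the hypothesised domains, with some favourable wording and no invitation to report no change or worsening, so perceived effects may lean toward benefit

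*Protocol article*

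**What the plan says.** The interview questions for both visits (post-intervention and one-year follow-up) are printed in Tables 2 and 3, under Outcome measures, Qualitative data.

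- **Participants, question 2** (experience of the program) has the prompts "Interviewer's prompts: satisfactory? stimulating? useful".
- **Participants, question 6** asks "Can you please tell me in as much detail as possible how you have been since practicing mindfulness", and **question 7** asks "From your perspective, how did your mindfulness practice influence your health and life". Both are followed by "Interviewer's prompts: cognitive function, psychological health, functional abilities and quality of life".
- **FSPs, question 6** asks how mindfulness has influenced the participant's health and life, then how useful it has been. The one-year wording is "How useful do you think mindfulness has been for him/her overall". The same four domain prompts stand directly beneath.

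Anticipated results describes the coding as "The iterative (repeating) and inductive (bottom up) process of thematic analysis". It warns that the numbers may show trends rather than significant results, and says the mixed-methods design "enables the qualitative findings to complement the quantitative results in greater depth".

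**The concern.** An interview about perceived effects should let a person report benefit, harm or nothing with equal ease. This guide names topics the investigators hope will improve, uses some approving words, and never offers no change or decline as an answer about health.

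That matters more here than in many trials. There is no control group (Study design), and the article expects that about 20 participants will probably not give a significant result (Potential pitfalls and counteracting measures). The same section justifies the smaller design partly by the richness of its qualitative data, so the interviews carry much of the interpretation.

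The interviewer is also the researcher who contacts participants weekly and then monthly to support their practice, administers the cognitive test, and interviews in the same session after the scales. Some participants with cognitive impairment may go along with a word offered by someone they know. The risk is that a theme partly prompted by the guide is later presented as separate support for a movement on a scale.

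**Working it through.** The article gives no figure on this point, so the check sets the text side by side.

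**1. Prompted topics against hypotheses.** Research questions hypothesises improvement in four areas: cognition, psychological health, mindfulness and activities of daily living. The domain prompts are also four.

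| Topic | Hypothesised | Prompted | Scale |
|---|---|---|---|
| Cognitive function | yes | yes | MoCA |
| Psychological health | yes | yes | DASS-21 |
| Functional abilities (daily living) | yes | yes | B-ADL |
| Mindfulness | yes | no | FMI |
| Quality of life | no | yes | none |

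So 3 of 4 prompted topics are hypothesised outcomes, and 3 of 4 hypothesised outcomes are prompted. The overlap is large but not complete.

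**2. Direction of the wording.**

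- Domain prompts at participant questions 6 and 7: bare topic labels. None names improvement and none names worsening.
- Stem of question 6: open, no direction.
- Stem of question 7: presumes that practice had some influence, but not which way.
- Prompts at question 2: 3 of 3 adjectives are favourable.
- FSP question 6: presumes a degree of usefulness, with the domain prompts attached to that framing.

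**3. Two-sided questions elsewhere.** Participant question 3 asks "What did you not like about the program", question 5 asks what made practice easier or harder, and question 12 is open. FSP question 4 asks for improvements to the program, and FSP question 8 is open. The two-sided items concern the program or the practice. None asks whether health stayed the same or got worse.

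**4. Against what the protocol itself foresees.** Stepwise procedures says that a participant's condition could hold steady, get better or progress to Alzheimer's disease. Intervention says the program or the data collection could cause worry or anxiety. The effect questions permit such answers, but none solicits them.

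**5. Against the analysis text.** Two researchers code and cross-check. The described coding does not separate what a person volunteered from what was said after a prompt. Interviews are recorded and transcribed verbatim, so that distinction can be recovered.

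**The case against.** The strongest reply is that the domain prompts are neutral labels under open stems. A participant prompted with cognitive function can say that memory is worse. That stands. A reader might infer that the interviewer supplies themes of benefit; the labels supply topics only. The evidence for favourable framing is question 2 and the FSP usefulness question, not the domain list.

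A reader might also infer that agreement between interviews and scales is built in. The document does not support this. Interview accounts and all the scales can move either way, one prompted topic has no scale, and one measured domain has no prompt.

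Third, inductive describes how transcripts are coded, and a semi-structured guide with topic prompts is compatible with that. This also stands; there is no contradiction to report.

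Fourth, the article says the two strands complement and inform each other. It does not claim independent corroboration, and exploring measured domains in depth requires asking about them. That is fair, so the point is a caution on interpretation rather than an error in the stated aim.

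Fifth, the guide has balancing questions, and the question 2 adjectives echo the study's own research question. The balance is real for the program and for practice. It does not reach health effects, and it shows that two-sided wording was available.

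**Conclusion.** The point holds in a limited form. The guide names three of the four hypothesised domains, uses only favourable adjectives at question 2, asks FSPs how useful mindfulness has been, and has no question or prompt on health effects that invites no change or worsening. Answers on perceived effects may lean toward benefit, and shared topics between themes and scales are not independent corroboration of a trend.

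The size of any lean is unknown. One could multiply out the guide: 4 topics × 2 questions × 2 visits × 20 participants = 320 prompted openings, and 4 × 1 × 2 × 20 = 160 for FSPs. A reader might take these as the scale of the bias. They are only ceilings: they assume that every prompt is used, that nobody drops out and that every participant has an FSP, which Recruitment says is not mandatory. They measure no bias.

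The conclusion assumes that the prompts are used at least some of the time and that a familiar interviewer's wording can influence answers. Both are plausible; neither is shown. No quantitative result is affected. This is an inexpensive improvement, not a flaw that undermines the study.

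**What to change.** 1. Make the existing prompts two-sided. At participant questions 6 and 7, for example: *cognitive function: better, worse or no different?*, and likewise for the other topics. At question 2: *satisfactory or not? stimulating or not? useful or not?* For FSPs at question 6: *how useful, if at all, and has there been any unhelpful effect?* The printed order, open stem first and prompts after, is already right and should be kept.
2. Tag each coded statement on perceived effects as spontaneous or prompted, working from the verbatim transcripts, and report perceived effects by that tag. Keep prompted reports: discarding them would lose prompted accounts of decline or no change, in people whose unaided recall may be limited.
3. State that overlap in topic between themes and scales is not, by itself, independent support for a quantitative trend.

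The cost is one extra tag during coding, somewhat more structured prompts, and rewording of a few lines. No added visits or staff are needed. If some interviews have already been held, the tag can still be applied to them; the report should then say which version of the guide each interview used.

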## Stepwise procedures

Altogether, there are a total of 3 data collection sessions in this study, which will be held at any of the Monash University campuses or a public venue such as library and community club that is convenient to the MCI participant and his/her FSP. The MCI participant will be administered the MoCA, the 21-item DASS-21, the 14-item FMI and the 12-item MAQ by researcher (WW) during these data collection sessions at three time points:

Pre-intervention (T1);Post-intervention (T2); andOne-year follow-up (T3).

These measurements should take about 30 min each session and will be conducted to compare the effects of mindfulness on the outcomes measures across these time frames and to determine whether any changes are sustained over time. By incorporating a 1-year follow-up into the study design, it could more effectively measure the longitudinal effects of mindfulness practice on persons with MCI over time. A semi-structured interview with the MCI participant that should take about 30 min, will be conducted by researcher (WW) at T2 and T3 after he/she has completed the above-mentioned cognitive assessment and questionnaires/scales.

The nature of the participants' MCI condition could possibly fluctuate between the time frames of provision of written informed consent (with their capacity to consent as confirmed by their FSP) and the 1-year follow-up period. In other words, their MCI condition could remain stable, improve or deteriorate to AD during the study duration. In the event that the MCI participant's MoCA score suggests severe cognitive impairment, his/her continued study participation will be reviewed and the referral to his/her GP or treating health professional for follow-up will be discussed with him/her and his/her FSP. Likewise, if the MCI participant reports a clinically significant DASS-21 score, the research team will contact him/her to ensure his/her well-being and seek his/her permission to inform his/her FSP and forward the score to his/her GP or treating health professional for follow-up. Any clinically significant information about the MCI participants collected from their study participation, will be stored in their health records with the participating CDAMS sites or communicated to their GP or treating health professional.

While the administration of the cognitive assessment and questionnaires/scales is in progress with the MCI participant during each of the three data collection sessions, the FSP will provide information about the MCI participant by completing the B-ADL Scale and the DHL questionnaire on his/her own. During T2 and T3, the FSP will be asked to attend a semi-structured interview that will take up to 30 min after the interview session with the MCI participant is completed. In sum, the FSP's study involvement duration during T1 is about 30 min, and during T2 and T3 is about an hour each. Should the FSP be unavailable to attend T2 and/or T3, he/she can return the completed B-ADL Scales and DHL questionnaires using reply paid return envelopes provided, and arrangements can be made for the interviews with the FSP to be conducted over the phone.

For an overview of this study, the stages of the study protocol are illustrated in Figure 1.

**Figure 1 F1:**
[figure not shown]
**Stages of study protocol**. Abbreviations (in alphabetical order): B-ADL, Bayer Activities of Daily Living (25-item); DASS 21, Depression Anxiety Stress Scales (21-item); DHL, Demographic, Health and Lifestyle questionnaire; FMI, Freiburg Mindfulness Inventory (14-item); MAQ, Mindfulness Adherence Questionnaire (12-item); MCI, Mild Cognitive Impairment; MoCA, Montreal Cognitive Assessment.

## Anticipated results

Repeated measures analysis of variance will be used to test the relative effects of formal and informal mindfulness practices on changes in the following dependent variables, namely cognitive function, psychological health, mindfulness, and ADL functioning from pre- to post-intervention and from post-intervention to 1-year follow-up, with an experiment-wise error rate of 0.05. Normally, each ANOVA should be evaluated with an adjusted (for e.g., Bonferroni correction) decision-wise error rate for possible inflation of Type I error. However, Type I error rate will not be adjusted for these analyses, on the grounds that this is an exploratory study of which any possible effects should be examined by further research. Regression analysis will be used to determine the predictive values of measures of formal and informal mindfulness practices on the changes in the same dependent variables (cognitive function, psychological health, mindfulness, and ADL functioning). Age, gender, and education will be entered into the regression analysis to identify possible moderating effects. The MCI participants' demographics, health and lifestyle information will be examined in relation to the outcome measures in order to interpret the results in context. However, possible trends instead of statistically significant results could be determined from the quantitative analysis. As such, the mixed-methods design of this study enables the qualitative findings to complement the quantitative results in greater depth so that their findings could inform each other and be integrated to better address the research questions. The IBM Statistical Package for the Social Sciences software package will be used for the statistical analysis of the quantitative data.

Qualitative data analyses by researchers (WW) and [name] (JC) will entail the investigation of the participant observational field notes and the semi-structured interview transcripts. To safeguard privacy, any identifiable information such as the name of the MCI participant, FSP, CDAMS, health service, GP and treating health professional in the audio recording of the interviews will be coded (but re-identifiable by the researchers for qualitative data analyses) in the interview transcripts. The QSR International NVivo software will be used to perform thematic analyses for the identification of important patterns/themes. The iterative (repeating) and inductive (bottom up) process of thematic analysis in the qualitative data analysis phase breaks the data into “smaller chunks” and assigns names or “codes” that summarize the idea within the data chunk (Hansen, 2006; Liamputtong, 2013). The codes are then refined by comparing, sorting and reflecting on the meaning and subsequently developed into “themes”^1^. A coding framework will be developed to provide definitions of the codes and maximize coherence among the codes for coding the qualitative data and generating themes or categories (Creswell, 2014). For inter-coder reliability, codes developed by researchers (WW and JC) will be cross-checked for agreement in coding with the same or similar code in order to maintain consistency in coding (Creswell, 2014). The framework of the presentation of both qualitative and quantitative data is illustrated in Figure 2.

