#### Quantitative data

The primary outcome is the change in cognitive function assessed by the Montreal Cognitive Assessment (MoCA) that measures the MCI participants' eight cognitive domains of visuospatial/executive, naming, memory, attention, language, abstraction, delayed recall, and orientation over time. The MoCA has excellent sensitivity of 90%, high test-retest reliability, predictive values, content validity and specificity, and good internal consistency (Cronbach's alpha of 0.83; Nasreddine et al., 2005). The MoCA will be administered by researcher (WW) during all three data collection sessions.

The secondary outcomes measured will be changes in psychological health, mindfulness and ADL functioning. The MCI participants will complete the following self-rated questionnaires during all three data collection sessions:

21-item Depression Anxiety Stress Scales (DASS-21) that measures psychological health on the axes of depression, anxiety and stress on a continuum of severity over the past week (high internal consistency with respective Cronbach's alphas of 0.94, 0.87, and 0.91; Antony et al., 1998); and14-item Freiburg Mindfulness Inventory (FMI) that measures the experience of mindfulness within the past 7 days (high internal consistency with Cronbach's alpha of 0.86, construct validity and sensitivity to change; Walach et al., 2006).

In addition, another secondary outcome measure of ADL functioning will be assessed using the 25-item Bayer Activities of Daily Living (B-ADL) Scale (Cronbach's alpha above 0.98) which will be completed by the FSP who will rate the MCI participant's functional deficits in the performance of everyday activities (Hindmarch et al., 1998; Erzigkeit et al., 2001).

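### The plan states an experiment-wise error rate of 0.05 for its repeated measures ANOVAs but declines the adjustment that would deliver it; 0.05 is a per-test level

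*Protocol article*

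**What the plan says.** The statistical plan is one paragraph under Anticipated results in the protocol article. It applies repeated measures ANOVA to changes in four dependent variables, "namely cognitive function, psychological health, mindfulness, and ADL functioning", over two intervals: before to after the programme, and after the programme to one year. The error rate is set in the same sentence: "from post-intervention to 1-year follow-up, with an experiment-wise error rate of 0.05".

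The paragraph then describes usual practice: "Normally, each ANOVA should be evaluated with an adjusted (for e.g., Bonferroni correction) decision-wise error rate for possible inflation of Type I error". It departs from that practice and gives a reason: "However, Type I error rate will not be adjusted for these analyses, on the grounds that this is an exploratory study", adding that any effects should be followed up in later research.

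Under Quantitative data, psychological health is measured by the DASS-21 on three axes (depression, anxiety, stress). The other three domains have one instrument each: MoCA, FMI and B-ADL. Neither section says how many ANOVAs or contrasts will be tested.

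**The concern.** The paragraph uses two terms and keeps them apart. The experiment-wise rate is the chance of at least one false positive over the whole set of tests. The decision-wise rate is the level applied to a single test. It names Bonferroni as the usual step that links the two, and then declines that step. So the experiment-wise wording cannot be dismissed as loose language for an ordinary 5% level: it states a property of the whole set of tests that the planned analysis does not have.

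Two things are at stake. First, the two sentences imply different significance thresholds for the same data, so an analyst can follow only one of them. Second, with about 20 participants and no control group, a single p-value below 0.05 among several outcomes could be reported as protected at 5% over the whole study when it is not.

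**Working it through.** **Inputs from the protocol article**

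- Stated rate: 0.05, experiment-wise (Anticipated results).
- Adjustment: none, so each test is run at 0.05 (Anticipated results).
- Outcome domains: 4 (Anticipated results).
- Intervals: 2 (Anticipated results).
- Scores if each DASS-21 axis is analysed separately: MoCA + 3 DASS-21 axes + FMI + B-ADL = 6 (Quantitative data).

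**Assumptions, because the article does not give them**

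- Number of tests k: 4 (one ANOVA per domain), 8 (4 domains × 2 intervals) or 12 (6 scores × 2 intervals).
- Correlation between test statistics: 0, or a common value of 0.5.

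**Formula.** For k independent tests at level 0.05 with no true change, the experiment-wise rate is 1 − 0.95^k.

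**When is the plan's figure reproduced?** With k = 1, 1 − 0.95 = 0.05. For any larger k, an unadjusted 0.05 does not give it. It is restored, slightly conservatively, by testing each at 0.05/k:

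- k = 4: 1 − (1 − 0.0125)^4 = 0.0491
- k = 8: 1 − (1 − 0.00625)^8 = 0.0489
- k = 12: 1 − (1 − 0.00417)^12 = 0.0489

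**Rate under what is planned**

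- k = 4: 1 − 0.95^4 = 1 − 0.8145 = 0.185
- k = 8: 1 − 0.95^8 = 1 − 0.6634 = 0.337
- k = 12: 1 − 0.95^12 = 1 − 0.5404 = 0.460

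**Allowing for correlation.** Outcomes measured on the same people will be correlated, which lowers the rate. Two-sided normal test statistics with a common correlation were simulated (400,000 draws):

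| Tests (assumed) | Independent | Correlation 0.5 | Correlation 0.9 |
|---|---|---|---|
| 4 | 18.5% | 15.6% | 9.3% |
| 8 | 33.7% | 25.0% | 11.9% |
| 12 | 46.0% | 32.0% | 13.4% |

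The two adjacent change scores share the middle time point, so a common positive correlation is not the only plausible pattern. With a correlation of −0.5 between adjacent changes, 8 tests give 31.7% if the outcomes are uncorrelated and 26.9% if they correlate at 0.5. For 12 tests the corresponding figures are 43.5% and 34.9%.

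Every case is above 5%. Only perfect correlation would bring the rate down to 5%, and four different instruments will not show that. The regression analyses planned in the same paragraph are not counted here.

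**The case against.** The strongest reply is that the paragraph misleads nobody who reads all of it. It raises possible inflation of Type I error itself, says what would normally be done, declines to do it and gives a reason. The study is a small uncontrolled pilot. Its section on potential pitfalls says that significance is unlikely and that the results may not generalise. No sample size or confirmatory decision depends on the 0.05. This stands: leaving exploratory tests unadjusted is a legitimate choice, it is disclosed, and it holds the severity down. It does not rescue the stated rate. Being exploratory justifies having no correction; it does not justify claiming the property that the correction would have provided.

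A second reply is that the test count is the reader's own. That also stands. With three time points, one repeated measures ANOVA per domain is a natural reading, and it gives four tests and about 16% to 19%. The contradiction does not depend on the count, but its size does.

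**Conclusion.** The statement of an experiment-wise rate of 0.05 is wrong as written, because the same paragraph rules out the step that would achieve it. What the plan delivers is 0.05 per test. The experiment-wise rate is then about 16% to 19% for 4 tests, 25% to 34% for 8 and 32% to 46% for 12. The lower figure of each pair assumes a common correlation of 0.5 and the higher assumes independence; the counts are assumed too. Severity is moderate.

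Three stronger readings are tempting and are not supported.

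- A reader might count 24 tests (6 scores × 2 intervals × formal and informal practice) and quote a true rate of 71%. That takes every possible split at once and assumes independence, and the article states neither.
- A reader might infer that the primary outcome ("The primary outcome is the change in cognitive function assessed by the Montreal Cognitive Assessment (MoCA") needs its own protected test, or one fixed interval. How alpha is allocated is commonly left to a statistical analysis plan, which is not shown here.
- A reader might take the remark that "possible trends instead of statistically significant results could be determined from the quantitative analysis" as a licence to claim success. No threshold for a trend is given. Alongside the admission that the small sample makes significance unlikely, the remark reads as well as an acknowledgement of low power leading into the mixed-methods rationale.

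**What to change.** Under Anticipated results, replace the experiment-wise statement with wording such as: *a per-test (decision-wise) two-sided level of 0.05, unadjusted for multiplicity, so the experiment-wise rate exceeds 0.05*. Interpret the results as exploratory, in line with the reason that the paragraph already gives. This changes wording only; the price is that the study no longer claims 5% control over the whole set of tests.

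Alternatively, keep the experiment-wise 0.05, state the number of tests k and adjust, for example to 0.05/k per test: 0.0125 for 4, 0.00625 for 8 or 0.00417 for 12. That costs power in a sample of about 20, and the sentence declining adjustment would have to go. Either route is coherent. The choice should be made before the data are analysed, because the two give different thresholds for the same results.
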